#### Data Management and Quality Assurance

Our research team is trained in the study requirements, measurement protocols, and has expertise in conducting physical assessments in solid organ transplant recipients. The research team has critically appraised the external peer-review comments from the Canadian Donation Transplant Research Program (Multimedia Appendix 1) and has incorporated them into the study protocol. Standard operating procedures have been generated for all the protocol elements. The accuracy of the data entered in our research database will be periodically audited by the research coordinator. The research team will attempt to have participants complete the entirety of the study assessments, and if there are incomplete data for a specific participant or missing responses to questionnaires, missing data will not be imputed. Participants will be closely monitored by the research team and the exercise professional to maximize study retention and assess exercise adherence rates during the 12-week intervention. Participants in the intervention group will be educated on the importance of adhering to the intervention, logging progress, and completing study assessments. The research team will send reminders to intervention participants for weekly meetings, and study assessments will be booked at convenient times for participants.

The study participants will have a random identifier generated with only the coded identifier attached to the participant data. The study data will be stored on a password-protected server following the currently established institutional and national research ethics and privacy guidelines. The study information will be accessible only to approved study members. In the event of an inappropriate release of personal health information to an unauthorized party, we will take the appropriate steps to minimize any potential harm: (1) further release of information will be stopped, (2) an attempt to retrieve all inappropriately released information will be made, and (3) the sponsor’s privacy office and research ethics board will be immediately notified.

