#### Study Arms

Following randomization, all study participants will be provided with a physical activity tracker (Fitbit) and exercise or physical activity logs to monitor exercise adherence and capture lifestyle changes in the intervention group and any contamination in the control group. Given the importance of diet on metabolic risk factors, both study groups will receive a counseling session on healthy eating consistent with the Canadian Food Guide by a registered dietitian, a review of the 3-day food record, and a nutritional handout. Nutritional advice will be tailored to specific metabolic concerns (eg, weight management, diabetes, and hypercholesterolemia). The dietitian will review all participants’ medical histories and pertinent bloodwork as routine care during dietary assessments.

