#### Intervention Group

##### Overview

Our exercise program was informed by expert guidelines on exercise prescription in solid organ transplant recipients [12,20,41] and will be delivered by an exercise professional with experience in chronic disease management. Following the baseline assessment and randomization, intervention participants will receive an individualized, home-based exercise program consisting of aerobic and resistance training exercises for 12 weeks. The exercise prescription targets the Canadian Physical Activity guidelines [42], which recommends ≥150 minutes of at least moderate-intensity aerobic training per week and at least two days per week of resistance training for major muscle groups. Daily exercise practice will be unsupervised; however, the exercise professional will provide the exercise prescription during the first training session via videoconference, including the following: an assessment of the participant’s ability to exercise independently in their home environment (eg, review of the participants’ heart rate, blood pressure, and history of any pertinent injuries), demonstration and review of training techniques, and proper use of their Fitbit and exercise equipment.

Participants will also receive a detailed manual describing the importance of exercise and self-management skills for exercise behaviors based on the theory of planned behavior and social cognitive theory adapted from previous studies [43,44]. The manual will highlight the basics of exercise training, the importance of routines, principles related to exercise progression, and photographs with descriptions of the prescribed exercises. After the initial training session, the exercise professional will follow up weekly (via videoconference) with study participants to address potential barriers to exercise, provide motivational support, review symptoms or adverse events during independent training at home, and prescribe training progression. The exercise program will be tailored to the specific and changing needs of the participant, taking into consideration comorbidities, exercise capacity, physical function, and availability of training equipment. Details on exercise prescription for the intervention group are briefly provided and described in Table 3.

**Table 3 table3:** Exercise prescription details for participants in the intervention group.

Modality and frequency	Intensity	Time and volume of exercise	Type of exercise	Progression

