#### Control Group

The control group will meet with the exercise professional at the start of the study to highlight the benefits of physical activity and will be provided with physical activity monitors (Fitbits) to track their daily physical activity levels (minutes and steps) along with physical activity logs to record daily physical activity. The study team will correspond with the control group every 2 to 4 weeks during the study period to see if any questions arise regarding the physical activity logs and trackers. After 12 weeks, the control group will have the option of receiving an exercise session with the exercise professional. During this session, study participants will receive general physical activity and exercise training recommendations and an exercise manual tailored to the needs of LTx and OLT recipients.

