##### Adherence

Adherence to the prescribed exercise program will be defined as completion of at least 70% of intervention components by the intervention group. This will be ascertained during weekly communication with participants and through a review of completed daily exercise logs, indicating exercise days, duration, intensity, and frequency of exercise sessions. Similarly, contamination in the control group will be assessed using physical activity logs.

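### Education on keeping logs and completing study assessments is assigned to the exercise arm only, although both arms must supply these data (minor, cheap to correct)

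*Protocol article*

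**What the plan says.** The sentence at issue is in the protocol article, Data Management and Quality Assurance: "Participants in the intervention group will be educated on the importance of adhering to the intervention, logging progress, and completing study assessments". No matching sentence is given for controls.

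The same section has three measures that name no arm:
- "The research team will attempt to have participants complete the entirety of the study assessments"
- "Participants will be closely monitored by the research team and the exercise professional to maximize study retention"
- the second half of this sentence, on booking: "The research team will send reminders to intervention participants for weekly meetings, and study assessments will be booked at convenient times for participants"

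The first half of that last sentence restricts reminders to the exercise arm, but for the weekly meetings only.

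Elsewhere:
- Study Arms gives both arms the recording tools: "all study participants will be provided with a physical activity tracker (Fitbit) and exercise or physical activity logs". It names contamination in the control group among their purposes.
- Adherence states that "contamination in the control group will be assessed using physical activity logs".
- Control Group describes a meeting at the start of the study and then correspondence: "The study team will correspond with the control group every 2 to 4 weeks during the study period to see if any questions arise". The questions meant are those about logs and trackers. Controls may also have an exercise session after 12 weeks.
- In the exercise arm, "the exercise professional will follow up weekly (via videoconference) with study participants" (Intervention Group, Overview).
- Retention is determined for the whole study and per group from completion of the final assessment, with an 80% criterion, and reasons for dropping out are collected (Retention).
- Between-group means with 95% CIs are to inform later sample sizes (Proposed Data Analyses), and missing data are not imputed (Data Management and Quality Assurance).
- Participants and the research team know the allocation (Randomization).

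**The concern.** The sentence joins three things. Adherence to the exercise programme exists in one arm only, so education about it has to differ. Logging and attending the assessments are data collection, and both arms do them. A measure that supports data collection should be the same in both arms, particularly where participants know their allocation.

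Three results depend on it:
- **Retention per group** is a feasibility outcome. If one arm is told why the final assessment matters and the other is not, a difference in retention reflects study procedure as well as acceptability.
- **The between-group 12-week estimates** rest on those who attend. Without imputation, a participant with no 12-week value does not contribute to the 12-week mean. If the arms lose different proportions, and those lost differ from those who stay, the difference is biased.
- **Contamination** is assessed partly from control logs, and controls who stop logging remove some of that evidence.

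**Working it through.** **1. Which measures differ by arm**

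| Measure | Exercise arm | Control arm | Should it be equal? |
|---|---|---|---|
| Education on exercise adherence | yes | no | no, part of the intervention |
| Education on logging | yes | not stated | yes |
| Education on completing assessments | yes | not stated | yes |
| Reminders for weekly meetings | yes | no such meetings | no, part of the intervention |
| Effort to complete all assessments | no arm named | no arm named | already equal |
| Monitoring for retention | no arm named | no arm named | already equal |
| Convenient booking | no arm named | no arm named | already equal |
| Tracker and logs | yes | yes | already equal |

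Only the second and third rows show an asymmetry in data collection.

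**2. The plan's own figures.** The sample size reproduces: 10 × 2 arms × 2 organ types = 40, or 20 per arm. The 80% retention criterion is 0.80 × 40 = 32 completers. There is no power-based figure to reproduce.

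**3. What the overall criterion allows.** Exactly 32 of 40 can arise as:
- 16 + 16 (80% and 80%)
- 18 + 14 (90% and 70%; Fisher exact p = 0.24)
- 20 + 12 (100% and 60%; p = 0.003)

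Power to detect 90% against 70% with 20 per arm is about 35%. Per-group counts would display an imbalance, but a test would often miss one of this size.

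**4. Possible bias (assumed inputs; neither the losses nor g are in the documents).** Let g be the difference in SD between those lost and those who stay, the same in both arms. Each completer mean shifts by (proportion lost) × g, so the bias in the difference is (difference in proportions lost) × g.

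| Losses in the two arms | g = 0.25 | g = 0.5 | g = 1 |
|---|---|---|---|
| 20% and 20% | 0 | 0 | 0 |
| 10% and 30% | 0.05 SD | 0.10 SD | 0.20 SD |
| 0% and 40% | 0.10 SD | 0.20 SD | 0.40 SD |

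For example, 0.30 × 0.5 − 0.10 × 0.5 = 0.15 − 0.05 = 0.10 SD. Exchanging the arms reverses the sign.

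**5. Scale.** The 95% CI half-width for a difference in means is t(0.975, n1 + n2 − 2) × √(1/n1 + 1/n2), in SD units. It is 0.72 at 16/16, 0.73 at 18/14 and 0.75 at 20/12. The bias at 10% and 30% loss (0.05 to 0.20 SD) is well inside that width.

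**The case against.** The strongest reply is that this is one sentence in a condensed article. Nothing says that controls are not told to complete logs and assessments, and the article states that standard operating procedures exist for all protocol elements. That would answer mere silence. Here the article assigns the education to a named arm, and the general wording about participants nearby does not remove that restriction. The cure is nevertheless only a clarification.

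Four stronger readings are tempting, and the documents do not support them.
- **That all measures to secure follow-up go to the exercise arm.** Three measures in the same section name no arm, and controls have their own contacts about logs and trackers. The reminders are for meetings that controls do not have.
- **That control logs are the only source on contamination.** Study Arms names the Fitbit alongside the logs, so a control who stops logging may still yield tracker data.
- **That contact frequency is the defect.** Over 12 weeks there are about 12 weekly contacts in the exercise arm, against 12/4 = 3 to 12/2 = 6 in controls. The weekly contacts are part of the intervention, and the fix would not change them.
- **That controls will drop out more.** The documents do not show this. The exercise arm carries the greater burden, and the optional session after 12 weeks may help to keep controls in. Leaving data unimputed does not by itself cause bias, as the equal-loss row shows.

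It also stands that retention is determined per group and reasons for dropping out are collected, so the counts in each arm would be visible. The pilot is not powered for the secondary outcomes.

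**Conclusion.** The point holds in a narrow form. One data-collection measure, education on logging and on completing assessments, is stated for the exercise arm only, although both arms keep logs and both owe the 12-week assessment. In an unblinded trial this could contribute to unequal follow-up or log completion.

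Neither direction nor amount can be derived from the documents. The illustrated bias rests wholly on the assumed losses and on an assumed dropout-completer difference, equal in both arms. It is small beside the pilot's own imprecision, though a wider interval does not remove a systematic error.

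Severity is minor: a cheap improvement, not a demonstrated design flaw.

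**What to change.** Reword the sentence in Data Management and Quality Assurance so that participants in both arms receive the same education and the same prompts on completing logs and the 12-week assessment. For controls, deliver this at the start-of-study meeting and within the 2- to 4-weekly correspondence already described under Control Group. Keep only the education on exercise adherence and the reminders for weekly meetings specific to the exercise arm.

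The cost is a change of wording and a few minutes in contacts that already take place. No extra visits or staff are needed.

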## Results

This research was funded in July 2020, and enrollment began in July 2021. It is estimated that the study period will be 18 months and that study assessment and data collection will be completed by December 2022. The study results will be submitted for publication in the first half of 2023.

## Discussion

### Overview

PTMS is a common sequela of solid organ transplantation and is associated with increased cardiovascular morbidity and mortality among LTx and OLT recipients [57,58]. Studies in the early posttransplant period (<1 year) have shown the benefits of facility-based exercise training on physical function and HRQL, but to date, only a recent study has evaluated the effects of 3 months of telehealth sessions on metabolic risk factors in OLT recipients [32]. These teleconferencing group sessions comprised alternating exercise and nutrition-based interventions with a few personalized sessions, which demonstrated improvement in PTMS, diet adherence, and mental HRQL. However, it remains unclear whether home-based exercise programs can be delivered with a sufficient exercise dose and adequate adherence to have effects on metabolic risk factors and exercise self-efficacy in both LTx and OLT recipients. This is an important consideration given the significant differences in routine perioperative rehabilitation practices across solid organ transplant recipients. For instance, LTx recipients participate in both pre- and posttransplant rehabilitation [41], whereas many centers do not have a dedicated exercise program for OLT recipients and may impact self-efficacy, adherence, and perception related to exercise training [12,59]. Thus, this protocol outlines the methodology of a pilot study implementing a partly supervised personalized home-based exercise program for LTx and OLT recipients as the first key step in developing future clinical trials to offset the high morbidity associated with PTMS.

### Home-Based Exercise Training

With fewer patients attending nonessential visits to health care centers during the COVID-19 pandemic, providing patients with tools to facilitate independent training has become a priority. There is increasing evidence that remote exercise interventions across a range of clinical populations have emerged in the last year [60-62], but more importantly in LTx and OLT recipients, showing promising results in training volumes and HRQL, respectively [26,32]. Furthermore, home-based interventions have become an important strategy in a number of chronic conditions and have the potential to be incorporated into the standard of care treatment plan for LTx and OLT recipients [63]. The novelty of the present home-based program lies in the promotion of exercise behaviors by increasing patients’ self-efficacy to exercise in a familiar environment with minimal equipment, resources, and supervision. Furthermore, home-based exercise training allows for reduced travel and increased convenience for participants to exercise in the comfort of their homes [26,32,64].

### Strengths and Limitations

Our study protocol has several strengths. First, we aimed to design a standardized, high-quality intervention grounded on theoretical and practical considerations specifically tailored for LTx and OLT recipients. The 12-18–month posttransplant period was chosen given the high rates of PTMS at this time point and the barriers experienced by patients [9,10]. We acknowledge that implementation of an exercise rehabilitation program early in the posttransplant period (eg, 3 months) may help prevent the occurrence of some of these metabolic risk factors, but we are specifically interested in addressing the knowledge gap of whether PTMS may be attenuated with a home-based exercise program in the late posttransplant period. Second, the home-based delivery format of this intervention constitutes a novel approach in the LTx and OLT populations. We prioritized implementation feasibility in the design of our protocol by creating an exercise program that can be replicated at home with minimal equipment and supervision while meeting safety parameters. Our intervention protocol was also designed to promote the sustainability of behaviors after the study period with exercises and activities that can be performed every day, such as walking, which also promotes transference to daily routines. Other highlights of our research include the inclusion of a control group, the rigor in our methodology (detailed and accurate reporting of methods according to the CONSORT, SPIRIT, and the Consensus on Exercise Reporting Template statements), and the inclusion of nutritional counseling for all study participants. Despite our trial being focused on exercise, we also acknowledge the importance of nutritional support in managing PTMS and made available a consultation with a dietitian as part of the educational component of our research.

We would also like to acknowledge the potential limitations of the study methodology. Given the complex profile of some of the patients diagnosed with PTMS, a 12-week intervention may not be sufficient to elicit a noticeable improvement in the metabolic profile of these patients. An extended intervention may have a greater impact on PTMS risk factors, insulin resistance, and physical function and will be considered in a future RCT. There is a potential risk of bias in our research given the lack of blinding of the exercise professional and study participants (double-blinding is often not achievable in exercise intervention studies) [65]. However, our study will aim to satisfy other aspects of the Revised Cochrane risk-of-bias tool for randomized trials [66]. Furthermore, we excluded patients diagnosed with unstable cardiovascular or neuromuscular disease to ensure participant safety and understand that this may reduce some of the generalizability across transplant recipients. We are also aware of the challenges to exercise training in this population (eg, osteoporosis and diabetes mellitus), and although we designed an exercise protocol achievable by most transplant patients, personalized adaptations of the intervention cannot be avoided and represent a key feature of our protocol. Finally, to facilitate the assessment of patients during the COVID-19 pandemic, we took steps to adopt our assessment protocol to provide participants with the possibility of performing study assessments from the participant’s home environment and bloodwork locally at community laboratories. We would like to acknowledge the potential threat to consistency in our assessment protocols, given that some assessments may be conducted on-site, whereas others will be performed remotely in the participant’s home.

### Conclusions

Exercise has become an important pillar in the management of comorbidities associated with LTx and OLT. A home-based exercise program may prove to be an effective posttransplant strategy for improving physical function and the metabolic profile of transplant recipients. Characterizing the feasibility, adherence, and effect estimates of home-based exercise training constitutes the first step in the promotion of a healthy lifestyle in transplant recipients and the establishment of long-term sustained change. This will be the first study to investigate the effects of exercise on PTMS risk factors, self-efficacy, and HRQL. The results of this trial can provide a greater understanding of behavioral strategies aimed at increasing exercise and physical activity in LTx and OLT recipients at risk of PTMS. Given the lack of patient education resources in the LTx and OLT populations, we hope that our results will provide greater insights regarding patients’ exercise preferences and exercise modalities to create patient-directed materials aimed at promoting healthy living after transplantation. Our research will create opportunities for future collaborations and initiatives to gain greater insights into the mechanisms of PTMS and reduce its high prevalence through lifestyle interventions.

## Appendix

Multimedia Appendix 1 Peer-review report from the Canadian Donation Transplant Research Program competition.

## Abbreviations

CONSORT: Consolidated Standards of Reporting Trials
HRQL: health-related quality of life
LTx: lung transplant
OLT: orthotopic liver transplant
PTMS: posttransplant metabolic syndrome
RCT: randomized controlled trial
RPE: rating of perceived exertion
SPIRIT: Standard Protocol Items: Recommendations for Interventional Trials
